## Abstract

**Background:**

In Bangladesh, seasonal influenza imposes considerable disease and economic burden, especially for those at high-risk of severe disease. The most successful approach for influenza prevention is the administration of a vaccine. Many poor and middle-income nations, including Bangladesh, do not have a national strategy or program in place for seasonal influenza vaccines, despite the World Health Organization’s (WHO) advice to prioritize high-risk populations. Additionally, there is a scarcity of substantial data on the cost-effectiveness of seasonal influenza vaccination in these countries. The aim of our study is to determine acceptability, health beliefs, barriers, and intention of receiving influenza vaccine among high-risk populations, assess the cost-effectiveness of implementing a facility-based seasonal influenza vaccination programme, and investigate the required capacity for a potential seasonal influenza vaccination programme.

**Methods:**

We will undertake this study following STROBE guidelines. We will conduct the study in inpatient and outpatient departments of three selected tertiary-level hospitals leveraging the ongoing hospital-based influenza surveillance (HBIS) platform. The study population will include the WHO-defined four high-risk groups excluding healthcare workers: children six months to eight years, pregnant women, elderly ≥ 60 years, and adults with chronic diseases. We will collect quantitative data on participants’ acceptability, health beliefs, barriers, and vaccination intentions using the health belief model (HBM) from patients meeting the criteria for high-risk populations attending two public tertiary-level hospitals. In one of the two public tertiary-level hospitals, we will arrange an influenza vaccination campaign before the influenza season, where the vaccine will be offered free of cost to high-risk patients, and in the second hospital, vaccination will not be offered. Both the vaccinated and unvaccinated participants will then be followed-up once a month for one year to record any influenza-like illness, hospitalization, and death. Additional data for objective two will be collected from patients with symptoms of influenza-like illness (ILI) and severe acute respiratory infection (SARI) at one public and one private hospital to determine both direct and indirect costs associated with influenza illness. We will estimate the required number of influenza vaccines, safe injections, and total storage volume utilizing secondary data. We will use a deterministic Markov decision-analytic model to estimate the cost-effectiveness of facility-based influenza vaccination in Bangladesh.

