## Background

Globally, Seasonal influenza is a major contributor to morbidity and mortality, resulting in significant health and economic consequences [1–3]. Based on data provided by the World Health Organization (WHO), it is estimated that influenza affects approximately one billion individuals annually [4]. Among these cases, 3 to 5 million individuals experience severe illness, resulting in 290,000 to 650,000 annual fatalities [4]. Low- and middle-income countries (LMICs) bear a disproportionately higher burden of influenza-related illness in comparison to high-income countries (HICs) [5]. Within LMICs, certain demographic groups are particularly vulnerable to experiencing severe illness as a result of influenza [5]. These groups include pregnant women, children under the age of five, the elderly, healthcare workers, and adults who have underlying health conditions [5]. Previous reports showed that older people were at higher risk of death and hospital admission during flu season [6]. The report also found that pregnant women and children were at higher risk of developing pneumonia and requiring hospital admission; the adults with co-morbidity conditions were at risk of hospitalization and intensive care admission during flu seasons [6].

To minimize the risk of influenza infection and reduce the severity of the associated illness, the World Health Organization (WHO) recommended in 2012 that persons at high risk of experiencing severe influenza symptoms receive an annual dosage of the influenza vaccine [7]. Despite the WHO recommendation of seasonal influenza vaccination prioritizing high-risk groups, 76% of the LMICs, including Bangladesh, lack a national policy/programme on seasonal influenza targeting high-risk groups [8, 9]. Notably, the WHO African Region (6.3%) and the WHO South-East Asian Region (18%) had the lowest proportions of countries having influenza vaccine policies [9].

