In Bangladesh, the influenza-associated mortality rate was estimated at six per 100,000 for under-five children and 41 per 1000,00 for persons > 60 years [17]. Also, the rate of hospitalization associated with influenza was estimated to be between 4.4 and 6.7 per 1,000 individuals in the population [18]. In contrast, the rate of influenza among outpatients with influenza-like illness (ILI) was estimated to be between 100 and 170 per 1,000 individuals in the population [18]. In 2010, approximately 25 million individuals across all age groups sought outpatient medical care for influenza in Bangladesh [3]. This resulted in an annual direct expenditure of US$ 108 million specifically attributed to influenza-related outpatient visits [3]. Moreover, approximately 30,592 laboratory-confirmed influenza patients of all ages were hospitalized each year, with an estimated annual influenza-associated hospitalization cost of US$ 1.4 million [3].

Influenza vaccines are the most reliable method for preventing influenza infection. Unfortunately, Bangladesh does not have a national influenza vaccination program among the WHO-recommended high-risk population [19]. The Ministry of Health and Family Welfare (MoH&FW), the Government of the People’s Republic of Bangladesh, provides complimentary influenza vaccinations exclusively to Hajj pilgrims [20]. This service is offered in adherence to the obligatory criteria set by the Saudi Government for all individuals participating in the Hajj pilgrimage [20]. However, there is a lack of information to drive the MoH&FW policy on influenza vaccinations in high-risk populations.

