### Study design

We will conduct our study leveraging the ongoing HBIS platform, a network of nine tertiary-level hospitals across Bangladesh [19, 25]. The structure and operational aspects of the HBIS platform have been previously discussed [19, 25]. Our study design will be quasi-experimental. To meet the vaccine acceptability objective, we will collect data on participants’ health beliefs, barriers, and vaccination intentions using the health belief model (HBM) from patients meeting criteria for high-risk populations attending two public tertiary-level hospitals. To meet the influenza vaccination cost-effectiveness objective, in one of the two hospitals, we will conduct an influenza vaccination campaign before the influenza season, where the vaccine will be offered free of cost to high-risk patients, and in the second hospital, vaccination will not be offered. Both the vaccinated and unvaccinated participants will then be followed-up once a month for one year to record any influenza-like illness, hospitalization, and death. Additional data for vaccination cost-effectiveness objectives on direct and indirect costs associated with influenza illness will be collected from ILI and SARI patients at one public and one private hospital. To meet the required capacity for a facility-based influenza vaccination objective, we will collect secondary data, including the Statistical Yearbook of Bangladesh 2020, as represented in Table 1 [26–28].

**Table 1 Tab1:** Assumptions and data sources by each target group

Target Group	Assumption and data sources
Children 6 months to 8 years, influenza vaccine doses	Two doses will be delivered, each four weeks apart [31, 32]. Data of the total number of < 5 years children will be adopted from the Statistical Yearbook of Bangladesh 2020 [26]. Monthly the number of children < 8 years visited hospitals will be collected from respected hospitals or respective District Civil Surgeon Office [29, 30, 33].
Pregnant women’s influenza vaccine doses	One dose to all pregnant women (any trimesters). The crude birth rate is assumed to be 21.9% (BDHS 2017-18) [34]. Influenza vaccines were distributed evenly across the childbearing years 15 through 49 [34]. Data on the total number of women of childbearing age (15–49 years) will be collected from the Statistical Yearbook of Bangladesh 2020 [26]. Monthly pregnant women who visited hospitals will be collected from respective hospitals or respective District Civil Surgeon Office [29, 30, 33].

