### Study population and participant recruitment

The study population will consist of persons belonging to the four high-risk groups as defined by the World Health Organization (WHO), except for healthcare workers: children six months to eight years, pregnant women, elderly ≥ 60 years, and adults with chronic diseases [7]. We have excluded healthcare workers from our targeted study population to prevent duplication with our prior research efforts [19]. We will enroll study participants who meet specific inclusion and exclusion criteria. Table 3 depicts the criteria utilized to determine the inclusion and exclusion of participants in our study.

**Table 3 Tab3:** List inclusion and exclusion criteria

Inclusion criteria	Exclusion criteria
Participants will be visiting study hospitals (outpatients and inpatients only. Not emergency departments) for routine care during the study period.	Participants with severe, life-threatening allergies to any ingredient in a flu vaccine (other than egg proteins)
Participants who will be children six months to eight years, or aged more than 60 years, or pregnant women (any trimester), or have any chronic disease such as chronic respiratory disease (requiring regular medication), diabetes, chronic renal disease, any cancer, excluding basal and squamous skin cancers, immune suppression or immune deficiency, chronic liver disease, chronic hematological disorder, chronic kidney disease, chronic neurological impairment/disease, serious mental health condition, organ or bone marrow recipient, history of any prior surgery, percutaneous coronary intervention, high blood cholesterol, family history of cardiovascular disease, other pre-existing conditions.	Participants having a history of severe allergic reactions (e.g., anaphylaxis) after a previous dose of influenza vaccine or to a vaccine component.
Participants /parents/caregivers who will be willing to sign the informed consent form	Participants having a history of Guillain-Barre syndrome less than six weeks after a previous dose of influenza vaccine.
Participants/parents/caregivers who will have an operational mobile phone number and are responsible for sharing updated phone numbers in case of plans to change for the next year	Participants having a history of moderate or severe acute illness with or without fever. The vaccine should be given after the acute condition has improved.

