#### Data sources for estimating influenza-associated disease burden

To estimate the key parameters of influenza-associated disease burden, such as the number of outpatient visits, hospitalization, and deaths, we will collect data from secondary sources [17, 26, 31, 34, 35, 54–58]: Table 1 represents the assumption and secondary data sources by each target risk group.

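### The child group is defined to age eight in one place and under five in another, and its model inputs cover different age ranges, so one child ICER cannot answer for the under-fives.

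*Protocol article*

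**What the plan says.** **The label.** The Abstract (Methods) states "The study population will include the WHO-defined four high-risk groups excluding healthcare workers: children six months to eight years". The section on study population and recruitment repeats it: the groups are "as defined by the World Health Organization (WHO), except for healthcare workers: children six months to eight years". The Background lists the groups vulnerable to severe illness differently: "These groups include pregnant women, children under the age of five, the elderly, healthcare workers, and adults who have underlying health conditions". The Background list and the recruitment section cite different sources.

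**Child inputs that stop at five.** The Background gives one child mortality figure: "the influenza-associated mortality rate was estimated at six per 100,000 for under-five children". Its source is among those listed for outpatient visits, hospitalizations and deaths in the section on disease-burden data. That section adds that "Table 1 represents the assumption and secondary data sources by each target risk group". In Table 1, in the row headed six months to eight years, "Data of the total number of < 5 years children will be adopted from the Statistical Yearbook of Bangladesh 2020".

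**Child inputs that go further.** The same row says "Monthly the number of children < 8 years visited hospitals will be collected". Table 5 sizes the effectiveness sample (465) and the cost sample (60) for six months to eight years. DALY estimates are described as age-specific.

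**The analysis unit.** Effectiveness is calculated for each risk group, and the Markov model is run 1,000 times for each risk group. No split of the child group is stated.

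**The concern.** The study is meant to inform national policy on vaccinating high-risk groups, and each group's ICER is judged against three times GDP per capita. On the Background's own list, the high-risk children are the under-fives. A pooled result from six months to eight years cannot say whether vaccinating them is cost-effective, whichever mortality rate is finally used.

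The mixed age ranges add a second problem. If effectiveness and cost describe one age band while deaths and population describe another, the ICER describes neither. Mortality may also enter twice: through DALYs, and through the productivity loss from deaths, which the plan bases on a baseline mortality rate.

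**Working it through.** The plan states no figure that can be reproduced here. The check sets the child age ranges side by side and then asks how large a mismatch could be.

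**Age range of each child item**

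| Item | Age range | Where |
|---|---|---|
| High-risk label | 6 months to 8 years | Abstract; Study population |
| High-risk list | under 5 | Background |
| Mortality, 6 per 100,000 | under 5 | Background |
| Population count | under 5 | Table 1 |
| Hospital visits | under 8 | Table 1 |
| Effectiveness sample (465) | 6 months to 8 years | Table 5 |
| Illness-cost sample (60) | 6 months to 8 years | Table 5 |
| DALYs | age-specific | DALY section |

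Outside the group definition and its labels, age eight appears only with the two-dose schedule and the Table 1 visit counts. It is nowhere justified as a risk boundary.

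**Share of the band aged five or more.** Assume equal numbers at each year of age. Let w = (top − 5)/(top − 0.5).
- Eight-year-olds included (top = 9): 4.0/8.5 = 0.47.
- Band ends at the eighth birthday (top = 8): 3.0/7.5 = 0.40.

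**Case A: the under-five rate is applied to the whole band.** Let r be mortality at five and over relative to under five. The documents do not give r. Overstatement = 1/[(1 − w) + w·r].

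| r | w = 0.47 | w = 0.40 |
|---|---|---|
| 0 | 1.89 | 1.67 |
| 0.25 | 1.55 | 1.43 |
| 0.5 | 1.31 | 1.25 |
| 1 | 1.00 | 1.00 |

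**Case B: the under-five count stands for the whole band.** It covers 5/8.5 = 0.59 or 5/7.5 = 0.67 of the target number of children, so the group is undercounted. For deaths, the under-five rate times the under-five count, divided by the true band total, is 5/(4.5 + 4r) for top = 9, taking the under-five rate as constant from birth. This is 0.59 at r = 1 and 0.77 at r = 0.5. It reaches 1.00 only at r = 0.125 and 1.11 at r = 0, because the count includes the first six months of life, which are outside the target group. Deaths for the full band are thus understated unless mortality at five to eight is very low.

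Cases A and B generally pull in opposite directions, and the plan does not say which applies, or whether either does.

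**The case against.** A reader might infer that all the child burden inputs stop at five, that under-five mortality will be applied to every child, and that deaths averted are therefore overstated by a known factor. The documents do not support this.

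- Visit counts are for children under eight, DALYs are age-specific, and cost and effectiveness are primary data over the full band. Only the stated mortality rate and the population count are confined to under-fives among the model inputs. The under-five cost of USD 70 serves sample-size planning only.
- No section says that the under-five rate will be used for all children. The burden section lists several sources without naming a child age band, and what they give for ages five to eight cannot be seen. An under-five rate times the Table 1 under-five count would give under-five deaths with no inflation.
- The upper factor of 1.9 needs no influenza deaths at all at ages five to eight. If rates are equal, there is no overstatement.

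Nor can it be concluded that the WHO label is wrong. The Background list is not attributed to WHO, its wording need not be exhaustive, and neither cited source is at hand.

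It is also fair to say that a condensed article may leave age-specific inputs to a fuller document, and that the cohort model's dependence on entry age does not rule out a split. That limits the finding to what is written. It does not remove the unreconciled definitions or the three child age ranges in a single row of Table 1.

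**Conclusion.** The point holds in limited form. The plan gives two definitions of the high-risk child without reconciling them, and names child inputs for different age ranges within a group for which it states one model run and no split at five. As written, the child ICER risks mixing ages and cannot answer for the under-fives.

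The direction and size of any error cannot be determined. The range of 1.0- to 1.9-fold overstatement applies only if the under-five rate is used for the whole band. Using the under-five count instead covers 59–67% of the band. Both rest on a uniform age distribution, and the first also on an unknown relative mortality. Confidence is medium. The change is worth making before the model is run, and the design itself is not called into question.

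**What to change.** 1. Reconcile the high-risk child definition across the Abstract, the Background and the section on study population.
2. State the age range of each child burden input (population, visits, hospitalizations, deaths) and use it only for that range. The under-five count includes infants below six months, about 0.5/5 = 10% of it under uniform age, so it also needs trimming for 6–59 months.
3. Report child ICERs and averted outcomes separately for 6–59 months and for five to eight years. Use under-five mortality only in the first, and rest the conclusion about high-risk children on that stratum.
4. Keep enrolment, the pooled child effectiveness and the pooled child illness cost. Sixty children would divide into roughly 32 and 28 (w = 0.47) or 36 and 24 (w = 0.40), too few for firm age-specific cost means. State as an assumption that both strata share these pooled values.

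The cost is one extra split in the model and tables, less precise results in each stratum, and a need for burden inputs at ages five to eight. If none can be found, limit the child ICER claim to under-fives.

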**Discussion:**

The results of this study will enable the National Immunization Technical Advisory Group and the Ministry of Health & Family Welfare of Bangladesh to decide what steps to take to develop and implement an influenza vaccination strategy targeting high-risk populations.

**Trial registration:**

The Clinicaltrials.gov registration number is NCT05996549. The registration for the protocol version 2.0 took place in August 2023, with the initial participant being enrolled in March 2022.

## Background

Globally, Seasonal influenza is a major contributor to morbidity and mortality, resulting in significant health and economic consequences [1–3]. Based on data provided by the World Health Organization (WHO), it is estimated that influenza affects approximately one billion individuals annually [4]. Among these cases, 3 to 5 million individuals experience severe illness, resulting in 290,000 to 650,000 annual fatalities [4]. Low- and middle-income countries (LMICs) bear a disproportionately higher burden of influenza-related illness in comparison to high-income countries (HICs) [5]. Within LMICs, certain demographic groups are particularly vulnerable to experiencing severe illness as a result of influenza [5]. These groups include pregnant women, children under the age of five, the elderly, healthcare workers, and adults who have underlying health conditions [5]. Previous reports showed that older people were at higher risk of death and hospital admission during flu season [6]. The report also found that pregnant women and children were at higher risk of developing pneumonia and requiring hospital admission; the adults with co-morbidity conditions were at risk of hospitalization and intensive care admission during flu seasons [6].

To minimize the risk of influenza infection and reduce the severity of the associated illness, the World Health Organization (WHO) recommended in 2012 that persons at high risk of experiencing severe influenza symptoms receive an annual dosage of the influenza vaccine [7]. Despite the WHO recommendation of seasonal influenza vaccination prioritizing high-risk groups, 76% of the LMICs, including Bangladesh, lack a national policy/programme on seasonal influenza targeting high-risk groups [8, 9]. Notably, the WHO African Region (6.3%) and the WHO South-East Asian Region (18%) had the lowest proportions of countries having influenza vaccine policies [9].

Moreover, influenza vaccine coverage remains low in LMICs. A systematic review of seasonal influenza vaccine coverage in LMICs revealed considerable variation in vaccination rates across different demographic groups [10]. Specifically, among children, the coverage ranged from as low as 2% to as high as 72% in these countries [10]. Similarly, the vaccination coverage among the elderly ranged from 10 to 70%, while pregnant women exhibited a range of 0–4% coverage [10]. Among healthcare professionals, the vaccination coverage varied from 20 to 56% in the LMICs under study [10]. The potential cause for the low vaccination coverage may be attributed to the suboptimal rates of influenza vaccine uptake [11–14]. Research conducted on populations at high risk for influenza revealed varying rates of influenza vaccine uptake [11–14]. Specifically, the uptake of the influenza vaccine was observed to be 33.3% among healthcare workers, 5.4% among elderly individuals, 27% among pregnant women, and 33.7% among adults with co-morbid conditions [11–14].

To identify challenges to promoting influenza vaccinations in LMICs, several studies explored various barriers to influenza vaccination, such as inadequate infrastructures to provide universal vaccination services and insufficient systems for evaluating, procuring, regulating, storing, distributing, monitoring, and administering the vaccine [15, 16]. Also, the lack of context-specific knowledge on the economic burden of influenza vaccines on high-risk groups, lack of medical socio-behavioral patterns, and socio-economic consequences of influenza have been identified as challenges for promoting influenza vaccinations in LMICs [15, 16].

In Bangladesh, the influenza-associated mortality rate was estimated at six per 100,000 for under-five children and 41 per 1000,00 for persons > 60 years [17]. Also, the rate of hospitalization associated with influenza was estimated to be between 4.4 and 6.7 per 1,000 individuals in the population [18]. In contrast, the rate of influenza among outpatients with influenza-like illness (ILI) was estimated to be between 100 and 170 per 1,000 individuals in the population [18]. In 2010, approximately 25 million individuals across all age groups sought outpatient medical care for influenza in Bangladesh [3]. This resulted in an annual direct expenditure of US$ 108 million specifically attributed to influenza-related outpatient visits [3]. Moreover, approximately 30,592 laboratory-confirmed influenza patients of all ages were hospitalized each year, with an estimated annual influenza-associated hospitalization cost of US$ 1.4 million [3].

Influenza vaccines are the most reliable method for preventing influenza infection. Unfortunately, Bangladesh does not have a national influenza vaccination program among the WHO-recommended high-risk population [19]. The Ministry of Health and Family Welfare (MoH&FW), the Government of the People’s Republic of Bangladesh, provides complimentary influenza vaccinations exclusively to Hajj pilgrims [20]. This service is offered in adherence to the obligatory criteria set by the Saudi Government for all individuals participating in the Hajj pilgrimage [20]. However, there is a lack of information to drive the MoH&FW policy on influenza vaccinations in high-risk populations.

For reducing the influenza disease burden, influenza vaccination has demonstrated significant efficacy and cost-effectiveness, particularly within populations at high risk of infection [21, 22]. The immune responses induced by influenza vaccines are typically specific to the particular viral strain. The presence of antibodies specific to a certain type or subtype of influenza virus typically offers minimal or no immunity against other types or subtypes. Furthermore, such antibodies usually do not protect against antigenic variants of the same virus that emerge due to antigenic drift. Vaccination can potentially induce a “back boost” of antibody titers specifically targeting influenza A(H3N2) viruses in the adult population. Influenza vaccines are administered on an annual basis due to the occurrence of antigenic drift and shift. The efficacy of these vaccines, which typically ranges between 40% and 60%, exhibits considerable variation across different settings and influenza seasons [10]. In addition, the findings of a systematic review indicated that out of the 118 studies examined, 22 studies demonstrated that influenza vaccination resulted in cost savings [23]. This study’s findings also stated that there were 13 studies reporting cost-effectiveness ratios of $10,000 per outcome, another 13 reporting ratios ranging from $10,000 to $50,000 per outcome, and three reporting ratios equal to or exceeding $50,000 per outcome [23]. Although the cost-effectiveness of influenza vaccination has been established, it is necessary to note that the applicability of cost-effectiveness parameters may vary across different countries due to variations in influenza disease profiles, unit costs of vaccination, and health system delivery mechanisms [24]. Hence, it is imperative to have country-specific estimates to allocate limited resources effectively.

Bangladesh lacks context-specific data on the acceptability, cost-effectiveness, and vaccination capacity needed for influenza vaccination among the WHO-defined high-risk population, which hinders informed vaccination strategies.

